## Abstract

**Background:**

Procedural burn pain is the most intense acute pain and most likely type of burn injury pain to be undertreated due to the physician’s fear of the adverse effect of analgesia and lack of anesthetist present. At our institution, in most of the cases, local burn detersion and debridement were performed at the ward level without any analgesics. This article describes a study designed to test the analgesia effect of a fixed nitrous oxide/oxygen mixture on burn dressing pain.

**Methods/design:**

The experiment was carried out in three centers. The patients were given a number from 1 to 240. A randomization list was produced by a statistician according to our preliminary study. Due to the severity of the pain suffered, ethically it was decided to help as many as possible, so patients given the letters A, B or C were treated using a canister with the appropriate letter containing preprepared nitrous oxide/oxygen mixture (NOOM). Those with D were given oxygen only, from an identical-looking canister labeled D. Neither patients, nor doctors, nor nurses, nor data collector knew what was in each canister, thus they were all blind. The nursing officer who implemented the intervention handed the doctors envelopes containing the patients’ name and allocation of A, B, C or D. Thus, patients receiving NOOM or oxygen were in the ratio 3:1. Parameters, including pain severity, blood pressure, heart rate, digital oxygen saturation and the Chinese version of the burn specific pain anxiety scale (C-BSPAS), were taken before, during and after dressing for each group. A video and audio record was taken individually for later communication coding and outcome analysis. Rescue analgesic was recorded.

**Discussion:**

Based on the findings from our previous qualitative study that physician’s reluctance to order narcotic analgesia is due to its adverse effect and from our pilot experiment, this study aims to test the hypothesis that a fixed nitrous oxide/oxygen mixture will promote better burn dressing pain alleviation and outcomes. Analyses will focus on the effects of the experimental intervention on pain severity during dressing (primary outcomes); physiological parameters, C-BSPAS and acceptance of both health care professionals and patients (secondary outcomes). If this model of analgesia for burn pain management implemented by nurses proves successful, it could potentially be implemented widely in hospital and prehospital settings and improve patients’ satisfaction and quality of life.

**Trial registration:**

(Clinical Trials Identifier: CHICTR-TRC11001690).

## Background

Burn injuries are caused by contact with flame, steam, hot fumes, hot liquid, a hot surface, electrical current, or extremely acidic or alkaline chemicals. In China, there are 5 to 10million burn victims each year [1]. Pain is the most common symptom in patients who have experienced burns that require hospital treatment. Severe pain can erode the will to live. Severe burns are among the most painful, devastating, sudden and unpredictable forms of trauma [2]. Acute pain from burns induces anxiety and reluctance by patients to participate in their wound care and rehabilitation, thereby increasing morbidity and extending their hospital stays [3]. Uncontrolled acute pain is also thought to contribute to long-term sensory problems, including chronic pain, paresthesias, allodynia, hyperalgesia, neuropathic pain, phantom skin syndromes and dyesthesias [4-6], associated depression [7], and is correlated with suicidal thoughts at the time of discharge from hospital [8]. The management of burns pain presents a major challenge to the pain practitioner. It is complicated by the fact that burn pain is of nociceptive and/or neuropathic origin and exposes a variety of temporal patterns: constant background pain, intermittent movement-related pain and procedural pain. Patients describe procedural pain as having an intense burning and stinging quality that may continue to a lesser degree but may be accompanied by intermittent sharp pain for minutes to hours after dressing changes. Procedural pain is more severe than background pain and can be excruciating without adequate analgesia. In China, doctors undertake burn wound care including wound washing, dressing and debridement, so they inflict pain and bear the duty to relieve pain for burn patients. Previous studies showed that in some areas of China, burn professionals pay much attention to burn recovery and wound healing. Such experience has advanced the skill of treating burn wounds to international levels, but inadequate attention was paid to the pain management of burns, resulting in untreated or undertreated pain. Our previous qualitative study showed that barriers to effective pain control resided with health care systems and physicians. Due to lack of burn pain management guidelines and assistance of an anesthetist, as well as the fear of adverse effects of analgesia, physicians administrated inadequate analgesia to burn survivors during the dressing and performed oligoanalgesia to children and the elderly by encouraging patients to endure pain [1]. Our recent retrospective study showed that there were 2,436 burn patients discharged from the burns center in a tertiary hospital in China from 1 January 2009 to 30 September 2011. The total hospital cost was ¥192,287,550.40, and the expenditure on medicine was ¥ 56,855,365.48, but only ¥55490.84 was spent on analgesics. The cost of analgesic accounts for 0.0976% of medication in China, whereas in Western countries analgesics account for 50% of the treatment cost. Nearly 60% (58.54%) of patients received oligoanalgesia during their hospitalization. Morphine prescription was zero. Studies have demonstrated multimodal and balanced analgesia were performed in managing burn wounds [9,10].

A China National Knowledge Infrastructure search of the Chinese-language publications from 1994 to 2011 was conducted using the keywords ‘burn pain’ ‘pain management’, and ‘pain control’. This search produced 898 results, of which 21 were found to be relevant to the treatment of burn pain. Seven of the twenty-one were reported using nonpharmacological intervention with three reported by our team using wrist acupuncture to relieve procedure pain for patients undergoing dressing [11]. Of these fourteen pharmacological approaches: seven were studied with a designed randomized control trial, three had placebo control with vitamin C or normal saline and three cases report of clinical administration of intravenous propofol, fantenly and morphine plus midazolam patient-controlled analgesia (PCA) (reported by anesthetists) [12]. Our previous qualitative study showed that pain suffered by burns survivors is untreated and poorly managed. Inadequate treatment of burn pain and inconsistency in practice has been well documented for nearly two decades. Insufficient education, fear of side effects and the economic factors, as well as political reasons and organizational background are major obstacles to progress in burn pain management in burn centers [1]. Our recent study showed that some health care providers in a burn center are also troubled by the dilemma of side-effects of opioids and patients right for freedom from pain. They expressed their apprehensions when facing the unique challenges including the repeated infliction of pain on already traumatized patients with therapeutic procedures. They also stated their willingness to control burn pain as well as their limited knowledge of burn pain management [the result has not published]. Therefore, Chinese burn physicians badly need a safe, effective and economic analgesia implemented by nurses to obtain the optimal control of burns procedure pain. Unfortunately, in China, due to the busy and heavy workload, doctors hardly have the time or interest to explore a burn dressing pain management regime [13].

However, nurses, being around patients’ bedsides and taking care of patients 24 hours a day, are concerned about patients’ comfort. Fortunately, we learned that diluted nitrous oxide is of analgesic effect, so we hypothesized that it may be the most suitable analgesic to meet the need of burn dressing pain management. The analgesia effect of a fixed nitrous oxide/oxygen mixture on burn dressing pain (AEFNOOMBDP) study is a nurse-led, patient-participated, multicenter randomized controlled trial. This article describes the rationale underlying the study, the AEFNOOMBDP study protocol, the design and administration of the study, and the planned analytic approach. Results from the study are expected to be published in 2012.

Nitrous oxide (N_2_0) is an inhaled anesthetic gas possessing analgesic properties at lower concentrations. It is an effective, short-acting analgesic with few side effects and is widely used in obstetrics departments and has also been used prior to a variety of minor surgical procedures [14-20]. Throughout the decade spanning the mid-1980s through 1990s, there was a surge of N_2_0 research in prehospital emergency medical service (EMS) systems across the United States [21-26]. N_2_0 possesses several properties that make it ideal for bedside use in the accident and emergency department. It is easy to administer, requires no intravenous access before its administration, and the patient may control the level of analgesia by removing the gas. It possesses a rapid onset of clinical effect (less than two minutes), and after termination of administration, its effect disappears almost as quickly. It has very few side effects, all of which are self-limited and are generally resolved with termination of exposure to the gas. N_2_0 is widely used in facilities possessing anesthesia services. The apparatus to deliver the gas is inexpensive and portable, and easy for nursing staff to manipulate. But its use in burn dressing pain analgesia alone is rarely reported. We hypothesize that nitrous oxide/oxygen mixture (NOOM) does not completely abolish the pain felt during wound dressing, but rather lessens the intensity and severity of any discomfort that is felt.

## Methods

### Study design

The study was designed as a multicenter double-blind randomized controlled trial to compare the analgesic effect of a preprepared NOOM by group UTO (receiving usual pain treatment and oxygen) (n = 60) and group UTN (usual pain treatment and preprepared NOOM) (n = 180) intervention on burn procedure pain in three burns centers under audit for quality control. Research members will be deployed to each study field for measurement taking and evaluating of the results. We choose to randomize individual patients and double-blind because pain threshold varies individually and also due to the placebo effect of the cylinder. The overall study design is depicted in Figure 1.

**Figure 1 F1:**
[figure not shown]
Study design.

### Patient eligibility, recruitment, consent, and randomization

Ethical approval was obtained from Shanghai’s Changhai Hospital Ethics Committee (CHEC2011-105). Verbally consenting patients completed a study enrollment pack containing a written consent form and a Chinese versioned burn specific pain anxiety scale (C-BSPAS). Patients eligible for enrollment in the study included all cognitively intact, Chinese speakers aged three to sixty-five from participating burn centers, selected for 1 to 70% of total body surface area (TBSA) burn and who reported moderate to severe burn dressing pain .TBSA was diagnosed by doctors. Moderate pain severity was defined as a score of four or greater (on a scale of zero to ten) for worst pain during dressing. Specific inclusion and exclusion criteria are presented in Table 1.

**Table 1 T1:** Patient inclusion and exclusion criteria

Inclusion Criteria	Exclusion Criteria
Aged 3 to 65, either male or female	Mental disorder, drug dependence and drug abuse
Participants sustained 1-70% of TBSA burns or other injury requiring dressing procedure	Unconscious and unable to express pain by Changhai pain scale (VAS)
Recent worst pain (during dressing) reported to be 4 or higher (on a scale of 0 to 10)	Abdominal distension or suspected bowel obstruction, air embolism, pneumothorax, decompression sickness, epilepsy, chronic obstructive pulmonary disease and acute respiratory infection, pregnancy, severe inhalation injury; pharmaceutical or pathological pulmonary fibrosis; Maxillofacial injuries
The participants are volunteers and written consent obtained	
Burns or injured area not affecting the vital signs and digital pulse oximeter monitoring	Disease involving ear, nose, larynges such as sinuses, middle ear, tympan graft

### Description of experimental and control interventions

Process of allocation concealment; The experiment was carried out in three centers. The patients were given a number from 1 to 240. A randomization list was produced by a statistician according to our preliminary study. Due to the severity of the pain suffered, ethically it was decided to help as many as possible, so patients given the letters A, B or C were treated using a canister with the appropriate letter containing preprepared NOOM. Those with D were given oxygen only, from an identical-looking canister labeled D. Neither patients, nor doctors, nor nurses, nor data collector knew what was in each canister, thus they were all blind. The nursing officer who implemented the intervention handed the doctors envelopes containing the patients’ name and allocation of A, B, C or D. Thus patients receiving NOOM or oxygen were in the ratio 3:1. A sample size of 240 was established and randomized into two groups, for which patients with at least moderate pain severity (worst pain, visual analog score, VAS > = 4 out of 10) during dressing were randomly assigned to receive usual pain treatment plus oxygen (UTO = 60) and usual pain treatment plus preprepared NOOM (UTN, n = 180) intervention two minutes before dressing based on the current clinical practice, respectively. For each group, intervention outcome including pain severity (VAS), blood pressure (BP), heart rate (HR), digital oxygen saturation (SpO_2_) and C-BSPAS were taken two minutes prior to intervention, during dressing, immediately after dressing, and 10 minutes after dressing. Video and audio recordings were taken individually for later communication coding and outcome analyzing. Rescue analgesic was recorded.

Blinding: The double-blind RCT list was held by a researcher. The researcher (a nursing officer), who held the randomizing list was blind too. The list only showed groups A, B, C and D, but did not indicate what treatment these letters stood for. Oxygen intervention was used as a control group. The rules were that the cessation of blinding would take place only after all the trials had been completed.

Indicators present for the expected change in pain between the control and treatment interventions will be examined. The anticipated pain score (VAS) during dressing will be reduced to three to five in the UTN group. The physical parameters such as blood pressure, digital oxygen saturation should be maintained within normal range in the treatment group. The anticipated C-BSPAS will be much lower in the treatment group than that in the control group, and both patients’ and doctors’ satisfaction with the use of the treatment intervention should be obtained after dressing.

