### Planned analytic approach

In subsequent publications, we will report results pertaining to the analgesic effects of NOOM on burn dressing pain. Primary outcomes will include: 1) pain severity during dressing, measured as the mean of average and worst pain, and 2) burns-dressing-induced anxiety. The physiological parameters and satisfaction of both health care providers and patients are considered as secondary outcomes. Finally, exploratory analyses will assess the interaction between the intervention and age, sex, and racial minority. The primary estimates of the effects of the intervention on each of these outcomes will come from repeated measure analyses, following the intent-to-treat principle.

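### The only scheduled pre-gas VAS precedes the dressing and is a weak baseline for pain during dressing; the closer entry score is not named in the analysis

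*Protocol article*

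**What the plan says.** All references are to the protocol article.

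- **Measurement times** (Description of experimental and control interventions). Pain VAS, blood pressure, heart rate, oxygen saturation and "C-BSPAS were taken two minutes prior to intervention, during dressing, immediately after dressing, and 10 minutes after dressing". The same section has patients receive the "intervention two minutes before dressing based on the current clinical practice".
- **Entry** (Table 1). Patients qualify on "Recent worst pain (during dressing) reported to be 4 or higher (on a scale of 0 to 10". The section on interventions repeats the threshold of 4 for those who were randomised.
- **Types of pain** (Background). Constant background pain is distinguished from pain caused by procedures: "Procedural pain is more severe than background pain and can be excruciating without adequate analgesia".
- **Expected result** (Description of experimental and control interventions). "Indicators present for the expected change in pain between the control and treatment interventions will be examined", followed by "The anticipated pain score (VAS) during dressing will be reduced to three to five in the UTN group". No starting value and no value for the oxygen arm are given.
- **Outcome and analysis** (Planned analytic approach). A primary outcome is "pain severity during dressing, measured as the mean of average and worst pain". Effect estimates "will come from repeated measure analyses, following the intent-to-treat principle". The article does not say how any pre-treatment pain score enters the model.

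**The concern.** A baseline is useful when it predicts the outcome. The outcome here is pain while the wound is being dressed, and the only pain reading scheduled before the gas is taken before the procedure begins. By the article's own account, pain outside the procedure is a different and milder pain. That reading may therefore say little about how much a given patient will hurt during dressing.

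A score of the right kind already exists. Every eligible patient has reported worst pain at a recent dressing on a 0 to 10 scale. Neither the measurement schedule nor the stated analysis mentions it.

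Two things are at stake. The first is precision: a prognostic score may be left out, or the weak one may be used in a way that adds noise. The second is how a reduction is to be read, because the anticipated value of 3 to 5 in the UTN group is described as a reduction without saying from what.

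**Working it through.** **Timing.** The pre-gas VAS is 2 minutes before the intervention, and the intervention starts 2 minutes before dressing: 2 + 2 = about 4 minutes before dressing. The article does not describe the patient's state at that moment, so pre-procedure pain is the safe label.

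**The plan's own figure.** Sample size determination gives 12 as sufficient for 90% power at two-sided 5%, and 240 on regulatory grounds. No difference or SD is stated, so 12 cannot be reproduced. Solved backwards with the normal approximation, 12 in total implies an effect of 1.87 SD if split 6 and 6, or 2.16 SD if split 3 and 9.

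**Precision at the planned size.** Inputs from the article: 60 oxygen, 180 gas, 90% power, two-sided 5%. Assumptions: the correlation ρ between baseline and dressing VAS, equal SDs at both times, and a true difference of 0.5 SD for the power column.

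- √(1/60 + 1/180) = 0.1491
- Detectable difference with no baseline = (1.960 + 1.282) × 0.1491 = 0.483 SD
- Variance factor: 1 with no baseline, 2(1 − ρ) for a change score, 1 − ρ² for a covariate. The SE factor f is its square root.
- Detectable difference = 0.483 × f; power = Φ(0.5 / (0.1491 × f) − 1.96)

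| Use of baseline | Assumed ρ | Variance factor | SE factor | Detectable (SD) | Power at 0.5 SD |
|---|---|---|---|---|---|
| None | – | 1 | 1 | 0.483 | 91.8% |
| Change from pre-gas VAS | 0.2 | 1.60 | 1.26 | 0.611 | 75.5% |
| Change from pre-gas VAS | 0.3 | 1.40 | 1.18 | 0.572 | 80.9% |
| Pre-gas VAS as covariate | 0.2 | 0.96 | 0.98 | 0.473 | 92.8% |
| Pre-gas VAS as covariate | 0.3 | 0.91 | 0.95 | 0.461 | 94.0% |
| Entry score as covariate | 0.5 | 0.75 | 0.87 | 0.418 | 97.2% |
| Entry score as covariate | 0.6 | 0.64 | 0.80 | 0.387 | 98.7% |

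**When a change score loses.** With equal SDs, 2(1 − ρ) > 1 exactly when ρ < 0.5. A repeated-measures model that takes the pre-gas reading as the first time point, and reads the effect as the arm-by-time contrast against it, is a change score in this sense. With unequal SDs the condition becomes ρ < (pre-gas SD) / (2 × dressing SD).

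**The expected value.** Entry requires recent worst dressing pain of 4 or more, and the expected UTN value is 3 to 5. The two ranges overlap from 4 to 5. They are also on different measures: entry uses worst pain, the outcome the mean of average and worst. The stated value therefore does not by itself describe a reduction from entry, and it names no oxygen-arm value to compare with.

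**The case against.** The strongest reply is that no change-from-baseline endpoint is planned. The outcome is pain during dressing, the expected change is framed as control against treatment, and a blinded, randomised oxygen arm is measured at the same moment. The rise in pain when dressing starts is common to both arms and does not bias their difference. This stands in full.

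It also disposes of three stronger readings that a reader might infer:

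- **That no pre-treatment measure of dressing pain exists.** Table 1 requires one. What is missing is its mention in the schedule and the analysis.
- **That a successful gas would show up as an increase, because a patient with little pain beforehand can only rise to 3 to 5.** This needs a comparison with the pre-gas VAS that the article does not specify.
- **That the 3 to 5 target can be met with no effect by patients who enter at 4 or 5.** It is an anticipated group value. No responder definition, test or decision uses it.

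Four further replies have weight. Covariates are commonly left to an analysis plan, which is not at hand, so the article does not show that the entry score is discarded. The correlations are assumptions. The entry score is recalled, comes from another dressing, covers worst pain only and is truncated at 4, all of which may lower its correlation with the outcome. And precision may not be the limiting factor, given that 12 patients were judged sufficient and 240 are planned.

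What remains is that the one scheduled baseline is poorly matched to the outcome, a better-matched score is at hand, and the sentence on the expected result names no comparator.

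**Conclusion.** The point holds as an inexpensive improvement in precision and clarity. It is not a flaw in the validity of the trial: the randomised UTN-UTO comparison of pain during dressing is unbiased with or without a baseline and, with none, can detect 0.48 SD at 90% power.

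The size is illustrative. If the entry score correlates 0.5-0.6 with the outcome, adjustment brings the standard error to 0.80-0.87 of its unadjusted value; the pre-gas VAS at 0.2-0.3 brings it only to 0.95-0.98. The article supplies none of these correlations, and the real gain may be smaller.

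The one use that would do harm is change from the pre-gas VAS. At an assumed correlation of 0.3 and a true difference of 0.5 SD, power would fall from 91.8% to 80.9%. The article neither plans this nor rules it out.

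**What to change.** 1. Write down the qualifying worst dressing-pain VAS and the date of that dressing before randomisation, and include the score as a covariate in the between-arm analysis of VAS during dressing. Specify this before the blind is broken.
2. Keep the pre-gas VAS as a pre-procedure reading. It may stay as a second covariate, but should not be the reference for a reduction in dressing pain.
3. Replace the one-arm expectation of 3 to 5 with the expected UTN-UTO difference in VAS during dressing.

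The cost is a score and a date on the enrolment form and a few sentences of wording. The score is already needed to judge eligibility, and a patient without it fails Table 1, so no patient is lost. The measurement schedule and the treatment stay as they are. For patients already enrolled, the value should be taken from screening records and not asked again after a treated dressing.

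### The letter list sits with a nursing officer, the role that also delivers the gas, and masking what the letters mean does not conceal the upcoming sequence

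*Protocol article*

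**What the plan says.** All of this stands in the protocol article, Methods, under the description of experimental and control interventions.

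- **Origin of the list.** "A randomization list was produced by a statistician according to our preliminary study". It covers patients numbered 1 to 240.
- **Custody.** "The researcher (a nursing officer), who held the randomizing list was blind too".
- **What the custodian can see.** "The list only showed groups A, B, C and D, but did not indicate what treatment these letters stood for".
- **Delivery and envelopes.** "The nursing officer who implemented the intervention handed the doctors envelopes containing the patients’ name and allocation of A, B, C or D".
- **Coding.** Letters A, B and C are canisters of the nitrous oxide/oxygen mixture (NOOM). For the control, "Those with D were given oxygen only, from an identical-looking canister labeled D".
- **Stated blinding.** "Neither patients, nor doctors, nor nurses, nor data collector knew what was in each canister, thus they were all blind".

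The section does not say who screened or enrolled patients, or that the custodian was kept apart from enrolment or delivery.

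**The concern.** Concealment and blinding protect against different things. Concealment stops anyone involved in entry from knowing the next assignment before the patient is committed to it. Blinding stops people from knowing the treatment afterwards. The section presents its routine as allocation concealment, but the one safeguard it gives for the custodian is a blinding safeguard: the letters are visible and their meaning is not.

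Protection therefore depends on the meaning of D staying unknown for the whole trial. If it is worked out, a person with the list knows which coming numbers are oxygen. If that knowledge then influences which patient takes which number, the arms differ before treatment starts. Neither blinded outcome assessment nor the intention-to-treat analysis named under the planned analytic approach corrects that.

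**Working it through.** **1. The plan's own figures.** 240 × 3/4 = 180 and 240 × 1/4 = 60. The stated arm sizes reproduce exactly. No sample-size or power figure bears on this point.

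**2. What the custodian knows.**
- Without the list, always guessing NOOM is right for 75% of patients.
- With the list but no key, the custodian sees four letters and cannot tell which is the control.
- With the list and D recognised once, every later assignment is known, because each letter has one fixed meaning throughout.

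**3. How soon a D patient is treated.** Assuming independent 3:1 draws, P(at least one D among m patients) = 1 − 0.75^m.

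| Patients treated | P(at least one D) |
|---|---|
| 4 | 68% |
| 8 | 90% |
| 12 | 97% |

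This is the chance that a D patient has been seen, not that D has been recognised. The Background section gives an onset under two minutes and an almost equally quick offset. The documents give no figure for how recognisable the effect is. The article does print the key, while its Discussion describes the trial as at an early stage and running in one of three centres.

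**4. Illustration of the consequence.** Assumed inputs, none of them in the documents:
- SD of dressing VAS is 2.0.
- On a share s of the 60 oxygen slots, the milder of two waiting patients is placed on oxygen and the other goes to NOOM.
- The severity seen beforehand has correlation r with dressing VAS.

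The expected minimum of two standard normal values is −0.564. The oxygen mean falls by 0.564 × 2.0 × s × r. The same number of more severe patients is spread over 180 instead of 60, so the NOOM mean rises by one third of that. Hence:

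bias = 0.564 × 2.0 × s × r × (1 + 1/3)

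| s | r = 1 | r = 0.5 |
|---|---|---|
| 10% | 0.15 | 0.08 |
| 25% | 0.38 | 0.19 |
| 50% | 0.75 | 0.38 |

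Standard error of the contrast = 2.0 × √(1/180 + 1/60) = 0.298, about 0.30 points.

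At s = 25% the bias exceeds one standard error if r = 1 and falls below it if r = 0.5. Milder patients on oxygen make NOOM look worse than it is; the opposite steering makes it look better by the same amount.

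**The case against.** Several stronger readings are tempting, and the article does not support them.

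- **That those enrolling patients could see the assignments.** No section says that a nursing officer screens, consents or enrols. Screening and enrolment interviews are mentioned without naming who held them. The link from list to entry is possible, not documented.
- **That one person did everything.** The text gives custody and delivery to the same role. It does not say that they were the same individual.
- **That the envelopes were made up by looking patients up on an open list.** The text says what the envelopes contained, not when they were prepared or whether they were sealed. A name added after a patient is bound to a number is compatible with sound concealment.
- **That the trial records a motive to steer.** "Due to the severity of the pain suffered, ethically it was decided to help as many as possible" is the reason given for the 3:1 ratio, not a description of how staff chose patients.
- **That the defect is independent of the coding.** Steering by treatment requires knowing that D is oxygen, and the article says that the list holder and the others it names were blind to this, with identical-looking canisters.

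These objections limit the point to a vulnerability. They do not remove it: custody lies within the delivering role, no separation is stated, the sequence of letters is visible to its holder, and one fixed letter for oxygen makes the mask easy to lose. Sealing and timing may be set out in a full protocol that is not shown, but the custody arrangement is stated in the article itself.

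**Conclusion.** The point holds as a weakness in the stated concealment routine, not as evidence that selection took place. Being blind to the letters' meaning does not conceal the sequence, and a single recognition of D would reveal all later oxygen assignments to anyone with the list.

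The possible size is illustrative: roughly 0.2 to 0.4 VAS points if a quarter of oxygen slots were steered, against a standard error of 0.30, in either direction depending on how patients were steered. It rests on an assumed SD, steered share and correlation, and on D being decoded and the knowledge reaching whoever matches patients to numbers. The change is worth making because it is cheap and two of the three centres had not started.

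**What to change.** Amend the concealment and blinding paragraphs as follows:

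1. The statistician who produced the list keeps it, away from all staff who enrol patients or deliver gas.
2. Centres receive only opaque, sealed, consecutively numbered envelopes with no names entered in advance.
3. Each patient takes the next number in strict order of consent.
4. The envelope is opened only after consent, the entry worst-pain score and the pre-gas readings are recorded.

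Apply this at the running centre now and at the other two before they start.

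The cost is a short amendment and a changed envelope routine. The statistician is already involved, so no extra staff are needed. The small downside is that the envelope step comes slightly later in the workflow.
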